## Abstract

**Background:**

Our pilot study has demonstrated improvements in health outcomes through participation in a new sport, light volleyball (LVB), among older adults. In response to the promising results of the LVB pilot study and the priority of allocating resources to the prevention of age-related fitness degradation by the Hong Kong (HKG) government, the present study aims to investigate the effectiveness of a LVB intervention on physical and psychological health attributes among older adults at a larger scale in HKG.

**Methods/design:**

This study will apply both quantitative and qualitative methods with a large sample (approximately 315 participants). We will adopt a randomized controlled trial (RCT) design to further evaluate the effectiveness of a LVB intervention on health outcomes against a comparison group, Tai Chi (TC), and a control group (C). Older adults will be eligible to join the intervention if they are (a) aged 65 years and above; (b) living in the community independently; (c) absent of diagnosed cognitive impairment; (d) not regular participants in a structured PA program for two years preceding the study; and (e) able to achieve a passing score on the Timed-up-and-go test (TUG) and Abbreviated Mental Test (AMT).

About 315 participants will be randomly assigned into 3 groups in 1:1:1 ratio. LVB group participants will receive 16-week LVB program; TC group will utilize a simplified 24-form Yang Style TC, and C group participants will be instructed to maintain their normal daily activity and join regular non-exercise social gatherings. Measurements will be collected before and after the intervention, and 6 months and 12 months after completion of the intervention.

**Discussion:**

This intervention, if effective, will enhance older adult’s physical and psychological health, and provide the data and evidence to support policymaking in relation to future PA promotion for older adults.

**Trial registration number:**

ChiCTR1900026657.

## Background

### Health needs of the local community

There is a continuous ageing trend in the population of HKG. In the forthcoming decades, the number of people in HKG aged 65 or above will increase to 2.16 million by 2031 and 2.56 million by 2041 [1]. Similar ageing trends are found in CHN [2]. According to the Prediction Report on the Development Trend of Population Aging in CHN, there were 241 million Chinese citizens aged 60 or above in 2017, about 17.3% of China’s total population. This figure will peak at 487 million, or nearly 35% in 2050. The ageing population presents substantive problems for social services such as reductions in the working-age population and increasing fiscal pressure on healthcare, social welfare, and other services for older adults [2, 3]. Owing to the effects of net medical inflation, population growth and ageing, and assuming the service enhancement continues with the historical trend, Hong Kong’s recurrent social welfare and health expenditure as a percentage of nominal GDP would increase from $56.9 billion and $52.4 billion in 2014 and 2015, respectively, and to $523.3 billion and $563.6 billion in 2041 and 2042, respectively [4]. A structural financial deficit may then strike within a decade in HKG due to the gradual increase in older adult’s social and health expenditure and reduction in working-age population [2, 3].

Despite the fact that the benefits of participating in physical activity (PA) are well documented [5], only about 30% of older adults aged 60 to 69 years, participated in sufficient PA in HKG and CHN [6, 7]. Age-related fitness degradation was also found in Chinese older adults [8]. Responding to the population ageing and its social implications, Governments [3, 9] have initiated programs to promote active ageing to enable older adults to stay active and remain healthy (e.g. offering older adults with diversified courses on an on-going basis, training for the trainers). Therefore, developing effective interventions (e.g., light volleyball in this study) is critical for promoting active lifestyles among older adults that can reduce the number of elderly adults becoming frail at an early stage.

Chase et al. [10] conducted a systematic review and meta-analysis to determine the effects of supervised PA (e.g., resistance exercise and aerobic PA) interventions on physical functioning among older adults and concluded that supervised PA interventions were effective at improving physical functioning (d = .45). Limitations of the reviewed twenty-eight studies were identified, as 1) few related studies from Asia; 2) small sample sizes with median control group size of 19 participants; 3) intervention duration did not meet the current World Health Organization (WHO) global recommendation of 150 min of PA per week [5]; and 4) lacking of control group or RCT study design.

In CHN, a systematic review [11] found promising evidence of the positive health benefits (e.g. mental and physical health, quality of life, and balance) of traditional Chinese sports [e.g., Tai Ji Quan (or Tai Chi), and Qigong] and PA among older Chinese adults. The limitations of previously reviewed studies suggest that larger scale interventions with prospective follow-ups, RCTs with representative and sufficiently powered samples, and the use of valid and reliable outcome measures are recommended for future research. Importantly, Guo and colleagues [11] mentioned that other than these mainstream activities, there are more than 900 types of Chinese sports/PAs (including the newly developed sport, LVB) in existence [12]. More research is needed to explore and evaluate the health impact of these non-mainstream activities. This is in line with the suggestion of Blewitt and Chockalingam [13], that further investigation should be conducted to identify new PA for older adults to gain the benefits of being physically active.

Qualitatively, Franco [14] reviewed the existing literature on older adult’s opinions on participation in PA. Among the 132 studies included, older adults valued PA participations and programs that emphasized “interaction with peers such as preferred group-based activity”, “professional instruction”, and “physical limitations such as discomfort and concerns about falling”. Similar themes about older adult’s perspectives on currently existing PA programs/interventions were found in Van Dyck et al. [15]. Furthermore, older adults who were interviewed suggested new PA (e.g., aquafitness or LVB in this study), not just regular activities like walking and cycling, should be selected as intervention activities. Likewise, the Hong Kong older adults also suggested interventions “providing more sport training classes (19.4%)” can help the promotion of Sport for All [7]. Based on the aforementioned considerations, we found that there is a gap between research and service relative to promoting active ageing.

### Scientific evidence supporting the strategies to address the needs proposed in this project

Among different types of PA, LVB is a new PA (also can be a sport) modified from traditional volleyball that may help reduce fitness-related degradation and increase PA among older adults. In contrast to traditional volleyball, LVB uses a lighter weight (LVB 150 g vs. traditional volleyball 250 g) and larger sized (LVB 80 – 83 cm in circumference vs. traditional volleyball 65-67 cm) ball. The LVB ball travels in the air at a lower velocity and for a longer time, which increases the playability and rally time among players during the games. It thus makes the LVB game more accessible to those with ageing-associated degradation (i.e. slow movements and reaction time, etc.). LVB, as a modified PA, is preferable to other traditional sports (even as it is adapted to older adults) because LVB is a non-contact and team-effort sport and is played with two teams separated by a net. These LVB features reduce the older adults’ likelihood of injury, such as falling, and these features address the recommendations of Franco [14] regarding factors that facilitate older adult’s participation in PA. Additionally, the LVB playing court (i.e., a standard-sized badminton court) is smaller than a standard volleyball court, which enables the promotion of LVB in sport facilities that normally have limited space in HKG. Moreover, with the popularity of the China National Volleyball team and annual HKG professional volleyball competition (i.e., FIVB Volleyball Nations League), volleyball is a traditional and popular sport in HKG. Volleyball is one of the sports taught in the school Physical Education curriculum in HKG and CHN. All of these factors favor LVB promotion in HKG in the future.

Studies in CHN indicated that older adults gained physical and psychological health benefits from regular LVB practice [16]. However, some limitations were found in these studies, such as unclear fitness component measurements and lack of control groups. In 2018, Leung et al. [17] conducted a quasi-experimental intervention to evaluate the effects of a 15-week LVB intervention on physical and psychological attributes among 78 Hong Kong older adults (≥ 60 years) by comparing LVB to a modified form of physical activity, rouliqiu (RLQ), and to a control group. Compared to the control group, LVB participants experienced significant improvements in agility, cardiovascular endurance, upper and lower extremity muscle strength, and physical activity enjoyment. Compared to their RLQ counterparts, participants in the LVB group demonstrated greater cardiovascular endurance, upper extremity muscle strength, and physical activity enjoyment. This pilot study suggested that the effectiveness of LVB on promoting older adult’s health should be further investigated using a larger-scale RCT, combined with follow-up measures in the community. Health practitioners may consider LVB as an adapted physical activity intervention to promote health outcomes in older adults in the future.

### Objectives

In response to the promising results of the LVB pilot study and the priority of allocating resources to the prevention of age-related fitness degradation in HKG, the present project aims to extend the aforementioned work, which is to investigate the effectiveness of a LVB intervention on physical and psychological health attributes among older adults in HKG. Specifically, the objectives of this study are:
compare the effects of a 16-week light volleyball (LVB) intervention program, with a TC program in terms of improving functional fitness among Chinese older adults aged 65 years or above;compare the effects of a 16-week LVB intervention program, with a TC program in terms of improving psychological attributes (i.e., resilience, physical activity enjoyment) among Chinese older adults aged 65 years or above;compare the effects of a 16-week LVB intervention program, with a TC program in terms of improving quality of life and balance among Chinese older adults aged 65 years or above; and.evaluate the effectiveness of both interventions from the participants’ perspective in order to gain insight into the links between intervention elements and outcomes (e.g., identify mediators and moderators of program success).

## Methods

### Study design

This study utilizes both quantitative and qualitative methods with a larger sample (approximately 315 participants). We will adopt a RCT design to evaluate the effectiveness of the LVB intervention on health outcomes against an active comparison group (TC), and a control group. TC is chosen as our active control group because both LVB and TC are whole-body exercises, originating from China, and both are suitable for older adults and benefit older adults’ health [17, 18]. Next, compared to team-based LVB, TC is an individual PA that may impact the health and quality of life of older adults differently (e.g. perhaps psychologically). Evidence about the association between social support and PA suggests that older adults with greater social support (e.g. less social isolation) are likely to continue exercising [19]. Others [20, 21] demonstrated that increasing amounts of social support in community based group PA interventions were associated with increasingly beneficial effects (e.g., social functioning) relative to PA intervention and program adherence. Additionally, TC is a very popular activity among Chinese older adults [7]. When LVB is promoted or becomes popular in Hong Kong communities on a larger scale during the later phases of this project, TC is a good candidate for the PA utilized by the active control group in the current study. Perhaps a comparison between LVB and TC may provide some insight about PA promotion among HKG older adults in the future. We hypothesize that the LVB and TC interventions will produce significant improvements in selected physical and psychological health attributes compared to the control group. We expect the LVB intervention to be at least as effective as the TC intervention in enhancing health outcomes in older adults.

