### Sample size calculation

We computed a projected sample size using a statistical power analysis by G power [25]. The analysis was based on effect size (Cohen’s d = 1–1.88) from a previous study showing significant improvement in functional fitness (Cohen’s d = 1.88) and physical activity enjoyment (Cohen’s d = 1) following a LVB intervention, a control, and a comparison group [17]. With a more conservative effect size (Cohen’s d = .5), a total sample of 237 older adults is required in this three-group design study in order to achieve a power of 80% at a significance level of 5%. Finally, we aim to recruit 315 participants (45 participants per center, 7 elderly centers are needed, 105 participants in each group) in total, with a 25% expected dropout rate [26].

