### Data analysis

Data will be analysed using SPSS 24.0 with a significance level of .05. To answer study objectives (a)-(c), generalized estimating equations (GEE) models will be used to analyse mean changes in outcomes over time among the three groups with adjustment for baseline characteristics showing statistically significant differences among the groups. GEE models was used in similar study such as Kekäläinen et al. [37] and it take into account the Intra-class correlation coefficient of responses within an elderly centre and correlations between repeated measurements in the same individual. In addition, the GEE models do not require complete data and can be fit even when individuals do not have observations at every time point. Descriptive statistics of the socio-demographic variables (e.g., frequency, M and SD) will also be computed.

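### LVB is expected to be at least as effective as TC, but the trial is sized and analysed only for differences, with no margin or confidence-limit rule

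*Protocol article*

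**What the plan says.** The Study design section of the protocol article makes two separate statements. On the active arms against control: "We hypothesize that the LVB and TC interventions will produce significant improvements in selected physical and psychological health attributes compared to the control group". On LVB against TC: "We expect the LVB intervention to be at least as effective as the TC intervention in enhancing health outcomes in older adults". The Discussion repeats both.

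The first three items under Objectives all name the LVB-TC contrast. The first is to "compare the effects of a 16-week light volleyball (LVB) intervention program, with a TC program in terms of improving functional fitness"; the second and third do the same for psychological attributes and for quality of life and balance.

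The Sample size calculation takes d = .5 as a cautious reduction of effects seen in an earlier LVB study and concludes that "a total sample of 237 older adults is required in this three-group design study in order to achieve a power of 80" per cent at the 5% level. Recruitment is raised to 315 for 25% dropout.

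For inference, the quantitative Data analysis section says that "generalized estimating equations (GEE) models will be used to analyse mean changes in outcomes over time among the three groups", and sets the level: "Data will be analysed using SPSS 24.0 with a significance level of .05". The article contains no non-inferiority margin, no confidence-limit criterion and no non-inferiority or equivalence test. It does not say how a non-significant LVB-TC result will be interpreted.

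**The concern.** The two statements in Study design need different kinds of inference. Superiority over control can be shown by a significant difference. Being at least as effective as TC needs evidence that any LVB deficit is smaller than some stated amount, and a difference test does not supply that when it comes out non-significant.

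Followed as written, the plan can support the LVB-TC expectation only if LVB proves significantly better. If the result is non-significant, the article gives no rule for what may be concluded, and the stated expectation invites the reading that it was confirmed. This affects the contrast named in every quantitative objective, in a trial whose Discussion says the data will inform policy on physical activity for older adults.

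**Working it through.** **Inputs.** Three groups, 1:1:1 (Study intervention). d = .5, 80% power, 5% level, 237 evaluable in total, 25% dropout (Sample size calculation). Sidedness is not stated; two-sided is assumed. The SD is set to 1, so all differences are in SD units. Clustering by elderly centre and repeated measures are ignored throughout.

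**1. Reproducing the stated size.** For an omnibus three-group F test, put the extreme means 0.5 apart and the third midway: f = 0.5/√6 = 0.204. At alpha .05 and 80% power this needs a total of 234.3, or 78.1 per group. Rounded up to 79 per group, that is 3 × 79 = 237, as stated. The pattern of means is my inference. A two-sided pairwise t-test at .05 would need 64 per group (192 in total) and does not match; at .025 it gives 234, which is close. Dropout: 237/0.75 = 316, against 315 stated. The figure is therefore sound for detecting a difference.

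**2. Pairwise power at d = .5.** With 79 per arm, a two-sided t-test at .05 has power of about 0.88.

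**3. Precision of LVB minus TC.** Standard error = √(2/79) = 0.159. The 95% half-width is 1.96 × 0.159 = 0.31 SD.

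**4. Chance of a non-significant result when LVB is truly worse** (two-sided t-test, .05, 79 per arm):

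| True LVB deficit (SD) | Non-significant |
|---|---|
| 0.20 | 76% |
| 0.25 | 65% |
| 0.30 | 53% |
| 0.40 | 30% |
| 0.50 | 12% |

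**5. Power to exclude a deficit when the programmes are truly equal.** The documents give no margin, so a range is assumed. Power = Φ(margin/0.159 − 1.96), one-sided .025:

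| Margin (SD) | Power at 79 per arm |
|---|---|
| 0.50 | 88% |
| 0.40 | 71% |
| 0.30 | 47% |
| 0.25 | 35% |
| 0.20 | 24% |

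The smallest margin with 80% power is (1.96 + 0.84) × 0.159 = 0.45 SD, nearly the whole planning effect.

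**6. Size needed for a tighter margin.** For 0.25 SD at 80% power: n = 2 × (1.96 + 0.84)²/0.25² ≈ 252 evaluable per arm. With three arms and 25% dropout this is 756/0.75 = 1,008 recruited.

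**The case against.** The formal hypothesis is superiority over control. The LVB-TC sentence is introduced as an expectation, the objectives speak only of comparing, and Study design says that the comparison may offer some insight. No non-inferiority design is declared, and a GEE difference analysis does answer a neutral comparison. How intervals are read is often left to an analysis plan, which is not at hand. All of this is fair, and it favours a fix by rewording. It does not remove the gap: the expectation is stated twice, and a margin drives sample size. The sample-size section gives its effect size, power, level and dropout on a difference basis only. A later plan could add a margin but could not supply power that the size lacks.

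Four stronger readings are tempting, and the documents do not support them.

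- **That a non-significant result will be misread.** Nothing in the article says so; it only leaves the possibility open.
- **That only p > .05 could support the expectation.** Significant LVB superiority would support it too.
- **That d = .5 is implausible between two active programmes.** The Background reports that LVB did better than another active programme, rouliqiu, on several outcomes among 78 people. If the three groups were about 26 each, a simple t-test would need an observed d of about 2.01 × √(2/26) = 0.56 for significance. That study was quasi-experimental and its comparator was not TC, so it does not establish d = .5 here, but it prevents dismissing it.
- **That the stated 237 or 80% is wrong.** The size reproduces, and pairwise power at d = .5 is about 88%.

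The non-significance rates also depend on the deficit chosen, falling to 30% at 0.40 SD and 12% at 0.50 SD.

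**Conclusion.** The point holds in limited form. The article expects LVB to be at least as effective as TC, but both its sizing and its analysis address differences, and nothing defines what would count as support short of significant superiority. At the planned evaluable size, non-significance is the more likely result for true LVB deficits up to about 0.30 SD. Only margins of about 0.45 SD or wider could be tested with 80% power.

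These figures rest on 79 complete cases per arm, a single unadjusted measurement, a two-sided 5% level (one-sided .025 for non-inferiority) and no clustering. The planned GEE uses repeated and partial data and centre correlation, so actual precision could be better or worse; the percentages are illustrative. No analysis or sample-size figure is shown to be in error. It should be fixed because it changes what may be concluded on the contrast named in all three quantitative objectives, but it is not a fatal defect.

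**What to change.** Keep superiority testing for LVB against control and for TC against control. For LVB against TC, choose one of two routes before data are seen.

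1. **Estimation (preferred).** Drop the at-least-as-effective statement as something to be concluded, in Study design and in the Discussion. Report LVB minus TC with its 95% CI, and state that p > .05 will not be read as equivalence or non-inferiority.
2. **Non-inferiority.** Fix and justify a margin now for each key outcome. With outcomes signed so that positive values favour LVB, make the claim only if the lower 95% limit of LVB minus TC lies above minus the margin. State the power for that margin at the planned size, using the second table above.

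The first route costs a few sentences and no extra participants; the LVB-TC conclusion becomes more modest. The second is free only if a wide margin or low power is accepted: a 0.25 SD margin has about 35% power as planned and would need about 1,008 recruits for 80%.

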### Study intervention (objective #1–3)

In order to answer project objectives (a)-(d), the study will adopt a RCT. About 315 participants will be randomly assigned into LVB group, TC group and control group in 1:1:1 ratio; this will be about 103 participants in each group. Data will be collected at baseline (pre-test), after a 16-week intervention (post-test), and 6 months and 12 months after the intervention is completed. The intervention will be based on the previous program specifically designed for older adults in LVB [17] and in TC [18]. Each program consists of 32 training sessions, with 2 × 90-min sessions per week. The duration of the proposed intervention is consistent with the recommendation of U.S. Department of Health and Human Services (HHS) for PA recommendations [22]. The LVB Group’s program will be delivered by registered coaches from the Light Volleyball Association of HKG (LVBAHK). Content for this program is designed by the project co-ordinator (PC) and LVBAHK, which was found to be effective for improving health of older adults [17]. The TC Group will utilize a simplified 24-form Yang Style TC that is designed for easy learning and mastery. Participants will be led by a qualified TC instructor, and they will replicate instructor’s motions, postures, and movement speed. Any incorrect performance will be rectified by the instructor in the class. During the intervention, the control group participants will be instructed to maintain their normal daily activity and join regular non-exercise social gatherings in order to balance the psychosocial effect (i.e., to maintain the internal validity of the study) of regular gatherings for the LVB and TC groups.

